## **FOLLOW-UP PROCEDURES**

### **Study Instruments**

Standard operating procedures and structured forms for clinical history, physical assessment, and data collection in English will be used by each study site. All study staff are familiar with English and health systems data collection in the country are routinely done in English.

### **Active Surveillance**

Study participants will be seen by a health care worker/investigator on days 0, 1, 2, 3, 7, 14, 21, 28, 35, 42, and thereafter 1 time per month for 12 months. A blood slide will be collected at every visit to check for parasitaemia, whether symptomatic or asymptomatic. In addition, patients will be contacted by phone weekly for 12 months to detect fever episodes and to stay informed about migration.

## **Passive Surveillance**

Patients will be advised to return on any day during the 12 months follow-up period if symptoms return and not to wait for the next scheduled visit day. In particular, parents or guardians should be instructed to bring children to the center at any time if they show any sign of danger (unable to drink or breastfeed, vomiting everything, presenting with convulsions, lethargic or unconscious, unable to sit or stand, presenting with difficult breathing), if they are still sick or if there is any cause for worry. The participants will receive a study card to alert the health care provider to the participation status. Participants should continue to receive the allocated treatment for the duration of the follow-up period.

The basic follow-up schedule is summarized in Annex V and VI. A case report form and an adverse event report form will be used to record the general information and clinical observations on each patient enrolled into the study. Recurrent malaria episodes will be entered in the standard reporting form. The appointment schedule will be clearly explained, and a follow-up card with a personal identification number will be provided in addition to the patient ID card.

All reasonable efforts will be made to find defaulters to ensure complete treatment and follow-up. While patients are encouraged to return on their own for scheduled follow-up visits, it is essential that provisions be made ahead of time for locating patients at home if they do not attend as requested. This requires obtaining detailed directions to the home during enrolment, and study team members familiar with the community will be responsible for home visits and means of transport for the patients. The schedule of treatment and follow-up examinations given in this protocol must be followed to ensure data integrity.

## **END-POINTS**

### **Outcomes and minimal differences**

#### **Efficacy end points**

The primary outcome of this study will be to estimate the efficacy of AL compared to AL+PQ, and CQ compared to CQ+PQ against vivax malaria at Day 28/42.

In addition, any episode of vivax parasitemia during the one year follow-up following parasite clearance will be considered a recurrence. Each recurrence will be treated in the same fashion as the initial episode, the patient remains in the treatment arm he or she has been randomised to for the duration of the follow-up period.

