## SUMMARY

Following the rapid development of significant drug resistance of *Plasmodium falciparum* (Pf) to chloroquine and then sulfadoxine-pyrimethamine, artemether-lumefantrine (Coartem or AL) was adopted as first line therapy in Ethiopia in 2004. According to the current national malaria diagnosis and treatment guidelines updated in 2012 [1], first-line treatment for uncomplicated *P. falciparum* infection is AL. First-line treatment for *Plasmodium vivax* (Pv) is chloroquine (CQ) alone in malarious areas and with primaquine in non-malarious areas at health center and hospital level. WHO recommends treatment of Pv with CQ or an artemisinin-based combination therapy (ACT) in combination with primaquine [2]. For all clinical infection without laboratory confirmation, AL is the first-line treatment since AL is effective against both Pf and Pv. Thus, in Ethiopia, where treatment for malaria without laboratory confirmation occurs frequently, Pv is often treated with AL as the standard of care. Similarly, the recommended drug for mixed infection with Pf and Pv is AL. Now with wide-spread use of AL and CQ and with evidence that malaria laboratory testing is occurring in about half of those suspected with clinical evidence of malaria infection, we propose to conduct an antimalarial efficacy study to monitor the effectiveness of these therapies in Ethiopia and to determine how efficacious these drugs remain for Pv. In addition, with high rates of relapse with *P. vivax* infection, the efficacy and safety of co-administering primaquine will be assessed. This information will inform future policy changes with respect to appropriate antimalarial strategies.

In this proposal, patients aged above 1 year with symptomatic malaria presenting to health centers will be enrolled for treatment with AL, AL+PQ, CQ, or CQ+PQ, for vivax infection. Phase 1 of the study will monitor the clinical, parasitological, and hematological parameters for *P. vivax* infection over a 42-day follow-up period, which will be used to evaluate drug efficacy. Phase 2 will continue monthly follow-up of these patients for one year to assess frequency of recurring vivax infections. Results from this research study will be used to assist Ethiopia in assessing their current national malaria drug policies.

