### For Primaquine:

- Number of vivax episodes following initial parasite clearance during the follow-up period.

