#### **Late treatment failure**

##### **Late clinical failure**

- danger signs or severe malaria in the presence of parasitaemia on any day between day 4 and day 28 (day 42) in patients who did not previously meet any of the criteria of early treatment failure;
- presence of parasitaemia on any day between day 4 and day 28 (day 42) with axillary temperature  $\geq 37.5$  °C (or history of fever) in patients who did not previously meet any of the criteria of early treatment failure

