##### **Late parasitological failure**

- presence of parasitaemia on any day between day 7 and day 28 (day 42) with axillary temperature  $< 37.5$  °C in patients who did not previously meet any of the criteria of early treatment failure or late clinical failure

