## **HANDLING OF UNEXPECTED OR ADVERSE EVENTS**

### **Response to new or unexpected findings**

All treatment failures will be treated with quinine as per the National Guidelines. If sufficient number of malaria cases are presenting to the clinic but enrolment is insufficient, the supervisor will need to determine at what point the problem with enrollment is occurring, and take steps needed to rectify the problem. If the problem is not remedied, the supervisor will report the poor enrollment to the investigators at CDC, Atlanta, and steps will be taken to either rectify the problem or to find a new site.

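### For a non-severe vivax recurrence up to day 42 the protocol orders both the allocated regimen and quinine, and does not say which prevails

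*Protocol*

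**What the plan says.** **Order to repeat the allocated regimen.** Under Efficacy end points, "any episode of vivax parasitemia during the one year follow-up following parasite clearance will be considered a recurrence". The next sentence gives the treatment: "Each recurrence will be treated in the same fashion as the initial episode, the patient remains in the treatment arm" to which he or she was randomised. Passive Surveillance points the same way in general terms: "Participants should continue to receive the allocated treatment for the duration of the follow-up period". Neither sentence carries a day limit.

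**Order to give quinine.** Late clinical failure is "presence of parasitaemia on any day between day 4 and day 28 (day 42) with axillary temperature" at or above 37.5 °C, or with a history of fever. Late parasitological failure is "presence of parasitaemia on any day between day 7 and day 28 (day 42) with axillary temperature" below 37.5 °C. For these patients, Response to new or unexpected findings says: "All treatment failures will be treated with quinine as per the National Guidelines". Emergency Care gives the quinine dose for any treatment failure or recrudescence, and Anticipated Benefits repeats the quinine rule. Annex VI, in the block for the day 3 to day 42 visits, calls for an alternative treatment on failure.

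**Outcome that depends on the choice.** The outcome for primaquine is "Number of vivax episodes following initial parasite clearance during the follow-up period". The Phase 2 objective compares this count between patients with and without PQ over 12 months.

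**The concern.** The two orders meet in the same patient on the same day. Someone who cleared the first infection and is slide-positive at the day 28 visit has both a recurrence and a late treatment failure. One rule gives chloroquine (CQ) or artemether-lumefantrine (AL) again, with PQ in the PQ arms. The other gives seven days of quinine. No sentence ranks one above the other.

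Two things are at stake. The first is patient care. None of the quinine instructions says whether PQ is continued, completed or repeated, although a failure on day 7 or 14 would fall inside the day 2–16 PQ course. The second is the meaning of the 12-month count. In the PQ arms it would describe either PQ with every episode, or one PQ course followed by quinine for an early recurrence with PQ left open. In the no-PQ arms the choice is between quinine and repeat CQ or AL. Treating clinicians know the allocation, so without a stated rule the choice could also differ between clinicians or arms.

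**Working it through.** **1. Where the two rules overlap**

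| Event | Recurrence rule (Efficacy end points) | Failure rule (outcome definitions, then quinine sections) | Conflict? |
|---|---|---|---|
| Early treatment failure, days 1–3 | Does not apply: precedes clearance | Quinine | No |
| Afebrile parasitaemia, days 4–6 | Allocated regimen, if cleared before | Not a defined failure (late parasitological failure starts on day 7) | No |
| Non-severe, with fever or history of fever, days 4–42, after clearance | Allocated regimen | Late clinical failure: quinine | **Yes** |
| Non-severe, afebrile, days 7–42, after clearance | Allocated regimen | Late parasitological failure: quinine | **Yes** |
| Severe malaria | Patient is withdrawn (withdrawal criteria) | Parenteral therapy (Emergency Care) | No |
| Any recurrence after day 42 | Allocated regimen | Failure no longer defined | No |

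**2. Whether another section settles it**

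- Rescue Treatment has the only time split, at 14 days. Up to then it names quinine. For later presentations it refers back to a therapy without naming it. If that is quinine, it contradicts Efficacy end points. If it is the initial regimen, it contradicts the sections that order quinine for all failures. Neither reading resolves the conflict.
- The note under Annex V allows rescue on any day when failure criteria are met, but is worded as permission and sets no precedence.
- Annex VI continues PQ through day 16 in the same block that calls for alternative treatment on failure, without connecting the two.

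**3. How many patients could meet the overlap**

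Inputs from Sample size determination: day-42 success of 68% with CQ and 58% with AL, a PQ reduction in relapse of at least 60%, and 120 patients per arm. The Introduction's 2009 data agree with the failure rates: 34/107 = 31.8% for CQ and 47/113 = 41.6% for AL.

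- CQ alone: 120 × (1 − 0.68) = 38.4
- AL alone: 120 × (1 − 0.58) = 50.4
- Without PQ: 38.4 + 50.4 = 88.8 of 240 (37.0%)
- CQ+PQ at a 60% reduction: 120 × 0.32 × 0.40 = 15.4
- AL+PQ at a 60% reduction: 120 × 0.42 × 0.40 = 20.2
- With PQ: 120 × 0.74 × 0.40 = 35.5 of 240 (14.8%)
- All arms: 88.8 + 35.5 = 124.3 of 480 (25.9%)
- Taking the stated 10–20% loss off in full: 124.3 × 0.90 = 111.9, down to 124.3 × 0.80 = 99.5

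These are all day-42 failures. They include early and severe failures, which step 1 puts outside the conflict and whose share the protocol does not give. The Introduction reports clinical cures lasting up to three weeks in all patients of the 2009 study, which suggests the early share is small.

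**The case against.** The best defence is that the protocol's structure supplies the rule. The Summary separates a 42-day Phase 1 from the longer follow-up: "Phase 2 will continue monthly follow-up of these patients for one year to assess frequency of recurring vivax infections". Efficacy end points gives the day-28/42 outcome first and introduces recurrences as an addition. Annex VI lists alternative treatment for the day 3 to day 42 visits and does not list it for months 2 to 12. A site could reasonably conclude that quinine applies up to day 42 and the allocated regimen after it.

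That reading is plausible and may be what was intended, which is why the remedy is small. But no sentence states it. The recurrence definition and the PQ outcome both start at parasite clearance, the Phase 2 objective counts over the whole 12 months, and the Annex VI block for any other day mentions alternative treatment without a day limit.

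A reader might also infer more than the documents support:

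- **That the primary comparison is compromised.** It is not. A patient's day-28/42 outcome is already determined at the first failure, before either re-treatment is given, and the comparison as randomised stays valid.
- **That every parasitaemia after clearance is caught.** Afebrile parasitaemia on days 4–6, severe cases and events after day 42 are not.
- **That Rescue Treatment clearly supports quinine throughout.** Its wording after day 14 is ambiguous and should not be counted for either side.
- **That the patient count measures bias in Phase 2.** It shows only how many patients might meet the two rules. The documents do not allow the size or direction of any effect on the episode counts to be derived.

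**Conclusion.** The protocol contradicts itself on the treatment of a non-severe vivax recurrence after clearance, from day 7 to day 42, or from day 4 with fever or a history of fever. This is more than missing detail that an analysis plan could supply: two stated dosing orders exclude each other.

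The overlap could reach up to about 124 of 480 patients before losses, about 89 without PQ and 36 with PQ. This rests on the protocol's own success rates, 120 per arm and a PQ reduction of exactly 60%. Because that reduction is stated as a minimum, 36 is an upper figure under the design assumption. The true number in conflict is lower by the unknown early and severe failures.

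The point should be fixed because it determines what a patient receives and what the 12-month episode count means. It does not touch the primary outcome.

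**What to change.** 1. Under Efficacy end points, add one sentence: re-treatment with the allocated regimen applies to recurrences after day 42, and treatment failures up to day 42 receive quinine.
2. In Rescue Treatment, name the drug for patients presenting after 14 days.
3. Align the sentence on allocated treatment in Passive Surveillance.
4. State whether PQ is continued, completed or repeated when quinine is given in a PQ arm.

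The cost is protocol wording and staff retraining. Sample size, outcomes and analyses do not change.

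If the investigators prefer the allocated regimen from day 15, then Response to new or unexpected findings, Emergency Care, Anticipated Benefits and the day 3 to day 42 block of Annex VI must be changed instead. That choice costs more, because each repeat PQ course adds directly observed visits. The choice of rule belongs to the investigators and the ethics committees; the protocol needs to state one.

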**Exclusion criteria for enrollment:**

1. General danger signs or symptoms of severe malaria (see Annex II)
2. Signs or symptoms of severe malnutrition, defined as weight-for-age  $\leq 3$  standard deviations below the mean (NCHS/WHO normalized reference values; see Annex III)
3. Slide confirmed infection with any other *Plasmodium species*. besides *P. vivax* mono-infection
4. Acute anemia, defined as Hg < 8 g/dl
5. Known hypersensitivity to any of the drugs being evaluated
6. Presence of febrile conditions caused by diseases other than malaria
7. Serious or chronic medical condition by history (cardiac, renal, hepatic diseases, sickle cell disease, HIV/AIDS)
8. Pregnant or breastfeeding women.
9. History of hemolysis or severe anemia
10. Regular medication, which may interfere with antimalarial pharmacokinetics (Annex IV)

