### **Laboratory Evaluations:**

2. Urine pregnancy test will be conducted on all women aged 13-49 and anyone testing positive will be excluded.
3. Those enrolled will have a second finger prick performed to assess for the following:
  - Thin smear will be used to verify parasite species and thick smear to conduct a formal parasite count. Two qualified microscopists will read all the slides independently. Blood smears with discordant results (differences between the two microscopists in species diagnosis, in parasite density of > 50% or in the presence of parasites) will be re-examined by a third, independent microscopist, and parasite density will be calculated by averaging the two closest counts.
  - Hemoglobin measurement (HemoCue™ Hb 301HemoCue, Angelholm, Sweden) will be carried out and those with hemoglobin <8g/dL will be excluded.
  - Filter paper will be obtained for the purpose of genotyping to differentiate identical vs. different genotypes, potential molecular testing for resistance markers, and gametocyte testing. G6PD testing using the NADPH fluorescent spot test will be conducted at the end of each day. The NADPH fluorescent spot test is a qualitative test and those determined to be G6PD deficient will not be given primaquine.
4. Patients testing smear positive for Pv will receive AL, at one site and CQ at the other site. After G6PD testing results are available, the patients not found to be G6PD deficient will be randomized to either AL alone or AL+PQ at one study site and CQ alone or CQ+PQ at the other site. Those found to be G6PD deficient will remain in either the AL or CQ alone arms. The study will not be blinded, although microscopists reading blood films will not be aware of which arm a participant is from.
5. On day 0, each patient will receive the morning dose of treatment (AL or CQ) medication under direct observation and will be monitored for vomiting for 60 minutes. The patient or parent will be given the evening dose (for AL only) to administer at home. Each patient will return on days 1 and 2 (and up to 14 days for those in the PQ arms) for subsequent doses. Those in the primaquine arms will return on every second day on days 2-16 for directly observed therapy. Clinical reassessments will be made on days 1- 3, 7, 14, 21, 28, 35, 42, and then monthly (see Annex V and VI for a table of scheduled procedures).

Participants will be given 35 Ethiopian Birr for each visit to cover their travel expenses (this is

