#### **Criteria for withdrawal/protocol violation**

Patients meeting any of the following criteria will be withdrawn:

- Withdrawal of consent
- Failure to complete the treatment
- Vomiting both initial and replacement doses at any single time in the treatment (i.e. If the patient vomits both attempts to administer the morning dose that would require withdrawal; however, vomiting the initial morning dose but not the morning replacement dose would not require withdrawal), persistent vomiting
- Severe side-effects necessitating hospitalization
- Progression to severe malaria
- Occurrence during the follow-up of concomitant disease that would interfere with a clear classification of the treatment outcome
- Antimalarial (or antibiotics with antimalarial activity) treatment administered by a third party or self-medication with antimalarial (or antibiotics with antimalarial activity- Annex IV) assessed by asking participants or their caretaker at follow-up visits
- Erroneous inclusion of a patient outside of the inclusion/exclusion criteria
- Misclassification of a patient due to a laboratory error (parasitemia) leading to the administration of the rescue treatment

Patients who are withdrawn will be followed up if possible and will be censored or excluded from the analysis. The reasons for discontinuation or protocol violation will be recorded on the case report form.

**Training for personnel:** Clinicians and laboratory personnel are trained and licensed in Ethiopia. In addition, they will receive approximately 1 week additional training to review the protocol of this study. In addition to technical aspects of specific laboratory techniques and clinical assessments, training will stress the importance of confidentiality, and appropriate techniques for obtaining informed consent. Continued appropriate processes with regard to informed consent will be reinforced by intermittent observation by the supervisor. The staff will include 1-2 laboratory technicians for microscopy, and 1-2 staff persons for enrollment and clinical assessments.

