**ANNEX V Schedule of follow-up activities**

|                                                                                             | Days |   |     |     |   |   |     |   |   |    |    |    |     |    |    |     |     |     |      | Months |  |
|---------------------------------------------------------------------------------------------|------|---|-----|-----|---|---|-----|---|---|----|----|----|-----|----|----|-----|-----|-----|------|--------|--|
|                                                                                             | 0    | 1 | 2   | 3   | 4 | 5 | 7   | 8 | 9 | 10 | 11 | 12 | 14  | 15 | 16 | 28  | 35  | 42  | 2-11 | 12     |  |
| Medical history, previous medication, physical examination, consent                         | X    |   |     |     |   |   |     |   |   |    |    |    |     |    |    |     |     |     |      |        |  |
| Pregnancy testing (if female age 13-49 years)                                               | X    |   |     |     |   |   |     |   |   |    |    |    |     |    |    |     |     |     |      |        |  |
| G6PD testing (Whatman 903)                                                                  |      | X |     |     |   |   |     |   |   |    |    |    |     |    |    |     |     |     |      |        |  |
| Primaquine , 14d                                                                            |      |   | X   | X   | X | X | X   | X | X | X  | X  | X  | X   | X  | X  |     |     |     |      |        |  |
| AL or CQ, 3d                                                                                | X    | X | X   |     |   |   |     |   |   |    |    |    |     |    |    |     |     |     |      |        |  |
| Vital signs                                                                                 | X    | X | X   | X   |   |   | X   |   |   |    |    |    | X   |    |    | X   | X   | X   | X    | X      |  |
| Parasite microscopy                                                                         | X    | X | X   | X   |   |   | X   |   |   |    |    |    | X   |    |    | X   | X   | X   | X    | X      |  |
| Hemoglobin                                                                                  | X    |   |     | X   |   |   | X   |   |   |    |    |    | X   |    |    | X   |     | X   |      | X      |  |

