#### Enrollment

Treatment, first dose with either AL or CQ  
Hemoglobin, filter paper for PCR  
Pregnancy testing, if female age 13-49 years

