**Month 2 through 12:**

---

Monthly blood sampling for subclinical parasitemia

Check hemoglobin at the end of follow up period (day 365)

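### Pregnancy is tested only on day 0, yet later vivax recurrences are re-treated with the allocated regimen, primaquine included, for 12 months without a re-check

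*Protocol*

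**What the plan says.** **At entry.** Item 8 of the exclusion criteria for enrolment reads "Pregnant or breastfeeding women". Laboratory Evaluations, item 2, puts the pregnancy part into practice: "Urine pregnancy test will be conducted on all women aged 13-49 and anyone testing positive will be excluded". Annex V marks that test under day 0 and no other column. Annex VI lists it ("Pregnancy testing, if female age 13-49 years") under Day 0, Enrollment, and nowhere later.

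**During follow-up.** Efficacy end points counts any vivax parasitaemia after clearance, within one year, as a recurrence. It then states "Each recurrence will be treated in the same fashion as the initial episode" and keeps the patient in the randomised arm throughout. Passive Surveillance repeats the point: "Participants should continue to receive the allocated treatment for the duration of the follow-up period". Under Drug Dosing and Regimens, PQ is 0.25 mg/kg daily for 14 days, and the only condition attached is a normal G6PD test.

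**Treatment failures.** Rescue Treatment, Response to new or unexpected findings, Emergency Care and Anticipated Benefits all give quinine for treatment failure. Failure is defined up to day 28 (day 42).

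**The concern.** The protocol applies its pregnancy and breastfeeding rule to the first treatment course and then stops applying it, although the same treatment can be given again at any time over 12 months. A woman in a PQ arm who becomes pregnant, or starts breastfeeding, after day 0 is no longer covered by any check when she has a recurrence.

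What is at stake is participant safety. The re-treatment rule leads to a drug being given to women whom the entry rule would have kept from it, and no planned procedure would reveal that this had happened. This is a gap between two rules, not a literal contradiction. The day 28/42 primary outcome is largely untouched, and no bias between arms is alleged.

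**Working it through.** The main check is a reading of the text, followed by a rough size.

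**1. Could any step detect a new pregnancy before repeat PQ?**

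| Place in the protocol | Content after day 0 | Pregnancy or breastfeeding addressed? |
|---|---|---|
| Annex V | Pregnancy test and medical history marked on day 0 only | No |
| Annex VI, Month 2 through 12 | "Monthly blood sampling for subclinical parasitemia" and a haemoglobin at day 365 | No |
| Annex VI, Any other day | Clinical assessment, temperature, parasitology, haemoglobin if indicated, alternative treatment for failure, blood spot | No |
| Annex VI, weekly phone calls | Fever and migration | No |
| Criteria for withdrawal/protocol violation | List of reasons for withdrawal | No |
| Methods to Minimize Risks | Follow-up for recurrence and haemolysis | No |
| Condition for giving PQ | Normal G6PD test | No |

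**2. When is the re-treatment rule unambiguous?** Up to day 28/42, parasitaemia can be classed as treatment failure, and the quinine rule then competes with re-treatment in the allocated arm. After that window only the re-treatment rule clearly applies. Taking day 42 as the limit:

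- 365 − 42 = 323 days; 323/365 = 88% of follow-up.
- Visits in that period are monthly, with 0 scheduled pregnancy checks.

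**3. How often would PQ be repeated?** The Introduction cites an Ethiopian study of CQ+PQ with 0.75% therapeutic failure by day 28 and 26.3% relapse by day 157.

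- 26.3 − 0.75 = 25.55 percentage points between day 28 and day 157.
- 25.55/26.3 = 97% of recurrences in that period fall after day 28.
- Planned PQ-arm patients: 2 × 120 = 240.
- 240 × 0.2555 = 61.3 patients.
- With 10% loss: 216 × 0.2555 = 55.2. With 20% loss: 192 × 0.2555 = 49.1.

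These counts cover both sexes and all ages. The two percentages are different life-table outcomes, so subtracting them is approximate. AL+PQ is assumed to behave like CQ+PQ, days 28 to 42 are still disputed, and the cited figures stop at day 157.

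**4. How many of these would be pregnant women?** The documents give no inputs for this. As an illustration only, assume that 20–35% of PQ-arm patients are women aged 13–49 and that 5–15% of them are pregnant at some point in the year:

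- 240 × 0.20 × 0.05 = 2.4 to 240 × 0.35 × 0.15 = 12.6 pregnancies.
- Times 0.263 with a recurrence: 0.6 to 3.3.
- If half of those recurrences follow conception (a further assumption): 0.3 to 1.7.

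**The case against.** There are five serious points on the other side.

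- **The annexes do not describe a recurrence episode.** They schedule no drug in months 2–12 either, so a missing pregnancy test there proves little. This is fair as to the weight of the annexes. But the body text does order re-treatment, and neither it nor the annexes order a check.
- **Treating a recurrence like the first episode could include repeating the entry checks.** The reading is possible but not compelled. The sentence is about treatment, names no test, and gives no action for a positive result. A rule that protects only under a generous reading needs rewording.
- **The exclusion is trial-wide, not specific to PQ, and the protocol states no PQ hazard in pregnancy.** Both statements are true. The finding needs only the protocol's own rule: such a woman could not have received PQ at entry, and later she can. The same gap exists for AL and CQ re-treatment, which is a reason to repeat the check in all four arms.
- **Unseen material may cover it.** The consent form, operating procedures and study forms are not shown and may carry advice. That cannot be ruled out, but it would not change the re-treatment rule as the protocol states it.
- **The number exposed is tiny and cannot be known.** This stands as to size. It does not remove the case for a cheap safeguard against an exposure that is preventable and would otherwise go undetected.

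**Conclusion.** The concern holds. Pregnancy is tested once, on day 0. Recurrences after day 28/42 are re-treated in the randomised arm for the rest of the year, and nothing in the protocol asks about, tests for or acts on a pregnancy or breastfeeding that began in between. Followed as written, such a woman in a PQ arm receives another 14-day PQ course.

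Repeat PQ courses are to be expected: roughly 49 to 61 patients between day 28 and day 157, if the cited CQ+PQ relapse figures carry over to both PQ arms. Exposures in pregnancy are probably few: 0.6 to 3.3, or 0.3 to 1.7 if half of the recurrences follow conception, both on assumed inputs. Exposure while breastfeeding should be rarer still. The point must be fixed on safety grounds, not because of any effect on the primary comparison.

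**What to change.** In Efficacy end points, with a matching exception in Passive Surveillance and entries in Annexes V and VI, require before every re-treatment course:

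- the existing urine pregnancy test for women aged 13–49, in all arms, and
- a question on breastfeeding.

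If either is positive, withhold PQ and treat under the National Guidelines. Screening Procedures for Enrollment already sends patients who are not enrolled to those guidelines. Their content for pregnancy is not visible here, so the amendment should name the regimen.

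Keep the woman in her randomised arm for the recurrence analysis and record the departure from allocated treatment. Do not process it as a withdrawal, because under that section "Patients who are withdrawn will be followed up if possible and will be censored or excluded from the analysis", and her later recurrences could be lost from the comparison.

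The cost is a short amendment and a few test strips at visits that already take place. The downside is that a few re-treatments will differ from the allocated regimen.
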